### Informed Consent

Participation in the study is voluntary, and participants are free to withdraw from the study at any time. All participants will provide written informed consent before data collection begins in the first home visit. The benefits, risks, and guarantee of confidentiality during data collection and information security for the participants are all explained in the consent form, in addition to the detailed explanation provided by the rehabilitation nurses.

### Intervention

The physical exercise program to be implemented is based on the OEP, including exercises aimed at improving balance, gait, and muscular strength in the lower limbs. The program is carried out by the elderly independently in their homes, supported by a paper-based manual, after in-person training with a health professional. In addition to the manual, the participants will have a common technological platform consisting of an Android tablet and a wearable sensor, which will enable them to access the OEP through interfaces with interactive feedback while exercising. This technological platform also allows interactive monitoring of the 5 strength exercises and 3 balance exercises (such as knee flexion, unipedal balance, and sit-and-stand).

In the first session at the participants’ homes, the rehabilitation nurse will train the participants to perform the exercises. Participants will be encouraged to carry out this program at least 3 times a week for 8 consecutive weeks. The rehabilitation nurse will provide participants with an in-person or telephone follow-up during these weeks.

The rehabilitation nurse will also instruct the elderly to wear comfortable clothes and shoes and inform the nurse if they experience joint or muscle pain. If such an event occurs, it is advisable to suspend the exercise.

Through the technological platform, the rehabilitation nurse will prescribe the OEP exercise plan for each participant, defining the exercises to be performed and the appropriate level of each exercise along with the frequency.

Each exercise session will have 3 sequential phases: warm-up phase, main phase, and relaxation phase with stretching exercises, which is a return to the calm phase. The progression in the exercises will be guided by the rehabilitation nurse and will be adapted to the functional capacity of the elderly. Regarding the intensity of the exercises, these will be performed without weights.

The OEP exercises and phases are explained in Multimedia Appendix 1. Throughout the duration of the program, participants will be followed up in person and by telephone by the rehabilitation nurse according to the intervention schedule (Figure 1).

**Figure 1 figure1:**
[figure not shown]
Intervention schedule.

### Outcome Measures

A rehabilitation nurse with professional experience will assess the participant at the baseline visit and after 8 weeks using a questionnaire and functional test assessment. In addition to sociodemographic or clinical (self-reported) variables and environmental risk variables, the data collection tool integrates primary and secondary outcome variables.

The primary outcome is gait (TUGT; normal step) [16]. The secondary outcome variables are lower limb strength and muscle resistance (30-second CST) [14], the 4 SBT, frequency of falls, functional capacity (Lawton and Brody - Portuguese version) [20], Falls Efficacy Scale International (FES-I) Portuguese version [21], usability of the technology (System Usability Scale [SUS] Portuguese version) [22], and environmental risk variables (home fall prevention checklist [HFPC] for older adults) [23].

The change over time in the participants is measured by improvement in the functional test scores.

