Recent studies have strived to integrate technology into physical exercise programs that were revealed as effective for adherence and overcoming barriers to exercise, as well as for improvements in health and independence [19]. Currently, several technological solutions address specific aspects of the fall cycle; however, the majority of these do not address fall detection, fall risk assessment, and fall prevention simultaneously. The FRADE (Pervasive Platform for Fall Risk Assessment, Detection and Prevention) project seeks to develop a common technological platform that allows the integration of all these components. This platform consists of the use of sensors that will collect data and monitor the gait of the elderly. This platform can also send caregivers alerts and text messages in the event of a fall. The tablet application provides a set of fall prevention exercises based on the Otago Program; along with a wearable sensor, it allows for the monitoring of user performance and evaluation of progress. This study aims to assess the impact of an exercise program supported by a technological platform on functional variables associated with risk of falling and assess the ease of use of this technology by the elderly.

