### Recruitment and Sample

Participants aged 65 years or older who were living at home in the district of Porto, Portugal were recruited based on the following criteria.

The inclusion criteria are able to walk independently; cognitive impairment, as assessed by the Portuguese version of the Mini-Mental State Examination (cut-off points of 22 for 0-2 years of schooling, 24 for 3-6 years of schooling, and 27 for ≥7 years of schooling); no severe visual or hearing impairment; and willingness to participate in a physical exercise program with technological support.

The exclusion criteria are a self-reported chronic or acute illness for which exercise is contraindicated, history of hip or knee surgery or lower limb fracture in the last 12 months, current or previous participation in physical exercise programs in the last 6 months, and participation in another research study involving fall prevention programs.

After approval by the ESEP ethics committee, the recruitment of participants will start through the Living COLABORAR Network. This network is part of a Fraunhofer Portugal research center, and it participates in an organization of institutions that give social, health, and leisure support and promote the well-being of their clients, especially the elderly. Potential participants will be contacted by Fraunhofer researchers who will present the study objectives and collect information from people interested in participating in the study.

Subsequently, those willing to participate will be scheduled for an evaluation conducted at home by a rehabilitation nurse in 2 phases. The first phase involves screening potential participants based on the inclusion and exclusion criteria. Consequently, the questionnaire prepared for this study will be completed. These participants will spend a part of their days in the community center, where they will become familiar with the tablets.

The convenience sample will include at least 30 participants.

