#### Technology Usability

Technology usability will be analyzed using the SUS. The original author of the test describes it as a quick tool to assess the usability of a particular product or service [42]. According to some authors, this test has several features that provide good assessment of the overall usability, such as the flexibility to evaluate interface technologies, interactive voice response systems, and hardware used in more traditional computer interfaces and websites. Ease and speed of use, both by participants and system administrators; ease of operation of scoring; and free access are characteristic of this test [43].

The original SUS consists of 10 statements that are scored on a 5-point Likert scale (Strongly disagree – Strongly agree). The final score can vary from 0 to 100 points, with higher scores indicating better usability [42]. In this scale, an excellent score is above 90; a good score is above 80, and an acceptable score is above 70; scores below 70 indicate usability problems [44]. In 2015, a group of Portuguese researchers [22] began the translation and cultural adaptation of this scale along with the subsequent evaluation of its metric qualities. The same authors stated that the SUS could be used to distinguish between usable and nonusable applications.

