### Statistical Analysis

Data processing will be carried out with SPSS software (IBM Corp, Armonk, NY). In the first approach, the data will be analyzed using descriptive statistics in order to classify the group of participants based on their sociodemographic, clinical, functional, and body processes data, using measures of frequency, central tendency, and dispersion. For inferential statistics, nonparametric statistics will be used, considering the sample size and sample type (nonrandom), with statistical significance set at *P*<.05. The prospective differences in the primary and secondary outcome variables, based on the 2 repeated measurements, will be tested using nonparametric tests equivalent to the *t* test for paired samples (Wilcoxon or McNemar procedure for quantitative and qualitative variables, respectively).

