## Discussion

The study will provide an objective measurement of fall risk factors and movement-based metrics obtained during the OEP exercises, such as strength of the lower limbs, mobility, and balance impairment

A quasi-experimental study protocol will be developed, focusing on the OEP, involving home-dwelling elderly, and using a common technological platform, with follow-up by a rehabilitation nurse 3 times a week over 8 weeks.

Throughout the intervention, the follow-up of participants through regular home visits, coupled with telephone contact, will contribute to better monitoring of the evolution of the condition of the participant and will increase their confidence and security, as a determinant for the recognition of the role of the nurses.

The technological platform will allow the centralization of all relevant variables in a unified and secured database, which will be accessible through a web portal and made available for the nurses supervising the study. In addition to the variables retrieved by the clinical application (eg, personal profile, medical conditions, medication, answers to the questionnaires, and scores of the 3 functional tests, the home application will allow the measurement of the range of motion along with the number of repetitions and durations of ascending and descending movements for the 8 exercises of the OEP, namely, knee flexion, knee extension, hip abduction, knee bending, toe raises, calf raises, sit-to-stand, and one-leg standing exercises. Previous studies have set a background for the technological solutions used in this study [45,46].

This study has some limitations, namely, the use of a nonrandom sample and the absence of a control group. Additionally, the recruitment process was hindered by the COVID-19 outbreak, even though all the National Health Service guidelines were followed. Additionally, the funding agency provided a relatively short time for the development of the study.

As for the technological aspect, we consider that the technological literacy of each participant may affect an individual’s use of the platform and that some limitations are likely to arise during the 8-week intervention program since some of the sessions will be performed by the elderly alone at home. To attempt to overcome these limitations, frequent contact between the nurses and the elderly will be established along with remote guidance whenever deemed necessary.

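### Week 8 is the only stated assessment after home use, so early withdrawers give no post-use usability score, and the score speaks only for a technology-willing sample

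*Protocol article*

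**What the plan says.** The Introduction of the protocol article gives as one of two aims to "assess the ease of use of this technology by the elderly". Outcome Measures lists "usability of the technology (System Usability Scale [SUS] Portuguese version") among the secondary outcomes.

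**Timing.** According to Outcome Measures, a rehabilitation nurse "will assess the participant at the baseline visit and after 8 weeks using a questionnaire and functional test assessment". No separate time is given for the SUS. Statistical Analysis states: "The prospective differences in the primary and secondary outcome variables, based on the 2 repeated measurements, will be tested using nonparametric tests". It makes no exception for the SUS. The Intervention section has the nurse train participants in the first home session, followed by 8 weeks of independent home exercise with nurse contact in person or by telephone. Informed Consent allows withdrawal at any time.

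**Scale.** Technology Usability says of the SUS: "The final score can vary from 0 to 100 points, with higher scores indicating better usability". It describes bands from the literature: above 70 acceptable, above 80 good, above 90 excellent, and below 70 a sign of usability problems.

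**Who is rated.** Recruitment and Sample requires "willingness to participate in a physical exercise program with technological support" and adds: "These participants will spend a part of their days in the community center, where they will become familiar with the tablets". The Setting section restricts enrolment to people who attend the community centre and live in their own homes. The Discussion grants that "the technological literacy of each participant may affect an individual’s use of the platform" and names the nonrandom sample and the missing control group as limitations.

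**The concern.** Two separate things can move the SUS result away from the question asked.

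**Missing ratings.** A usability score is informative only once someone has used the product. The one stated assessment that follows home use comes at the end of the 8 weeks. A person who leaves the study in week 2 or 3 because the tablet or sensors were too difficult has formed an opinion, but has no scheduled occasion to record it. If such people would rate the platform lower than those who stay, the observed mean is too high. The SUS is described against absolute bands and there is no comparison group, so an error of this kind does not cancel out. It moves the score directly relative to 70.

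**Target population.** Even with no withdrawals, the raters are people who agreed in advance to technological support, attend one community centre and become familiar with tablets there. The aim is worded for older people without qualification. A favourable score from this sample is probably higher than one from people without these features, and it does not answer the question for them.

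A smaller matter of timing goes with the first point. Taken literally, the analysis section pairs a baseline SUS with the week-8 SUS. A baseline SUS precedes the weeks of home use, so the difference would not measure a change in experienced usability.

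**Working it through.** The article gives no expected SUS score, dropout rate or SUS-based sample size, so there is no stated figure to reproduce. The check has two parts.

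**1. When can a post-use SUS be recorded?**

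- Stated assessments: baseline and after 8 weeks (Outcome Measures).
- Training takes place in the first home session, and home use runs over the next 8 weeks (Intervention). Baseline therefore comes before the period of home use.
- Withdrawal is possible at any time (Informed Consent).

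Of the two stated times, only week 8 follows home use. A participant who withdraws before then has no stated post-use SUS. A participant who stops using the platform but stays in the study can still be rated at week 8.

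**2. How far could the mean move?**

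From the documents: N = 30 (the minimum in Recruitment and Sample) and the band limit of 70 (Technology Usability). Assumed: the share d who start but give no rating, the mean R among raters, and the mean S that non-raters would have given.

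- Mean over all starters = (1 − d) × R + d × S
- Upward bias of the raters' mean = d × (R − S)
- Share at which the all-starter mean reaches 70: d* = (R − 70) / (R − S)

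All-starter mean with R = 75 (bias in brackets):

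| Non-raters of 30 | S = 40 | S = 50 | S = 60 |
|---|---|---|---|
| 3 (10%) | 71.5 (3.5) | 72.5 (2.5) | 73.5 (1.5) |
| 6 (20%) | 68.0 (7.0) | 70.0 (5.0) | 72.0 (3.0) |
| 9 (30%) | 64.5 (10.5) | 67.5 (7.5) | 70.5 (4.5) |

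Example: 6 non-raters with S = 40 give (24 × 75 + 6 × 40)/30 = 2040/30 = 68.0.

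Share at which a rater mean of 75 falls to 70:

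- S = 40: 5/35 = 14%, or 0.143 × 30 = 4.3 people
- S = 50: 5/25 = 20%, or 6 people
- S = 60: 5/15 = 33%, or 10 people

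With a higher assumed rater mean, R = 82, the all-starter mean stays above 70 in every cell of the same grid except 9 non-raters with S = 40: (21 × 82 + 9 × 40)/30 = 2082/30 = 69.4.

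If d = 0, or if S = R, the bias is zero.

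The second issue, who is eligible and familiarised, does not enter this arithmetic. It stands even when all 30 are rated.

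**The case against.** The strongest case on the other side is that the missing-rating problem is partly conjecture. Most of its individual points are fair.

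- A reader might infer that the SUS is taken only at week 8. The article does not say so. Read literally, the analysis section implies two measurements of every secondary outcome, and the intervention schedule and data collection instrument are figures not shown here, which may give the SUS timing. What stands is narrower: week 8 is the only stated assessment after home use.
- A reader might infer that people who give up on the platform never rate it. The documents do not support that. Participants also have a paper manual, so someone can set the tablet aside, continue exercising and give a low SUS at week 8. Nothing limits that assessment to platform users. Only those who leave the study early are affected.
- How withdrawals are analysed may properly be left to a fuller document. That is accepted and not held against the article. The point here is when the score is collected, because analysis cannot recover a rating that was never taken.
- Willingness is close to what consent already requires, and it is not the same as skill. The familiarisation excludes nobody, and the article does not date it, so it cannot be called a run-in before entry. Both points are accepted. They leave the limit on generalising in place.
- The Discussion concedes that technological literacy may matter and plans frequent nurse contact, and the home application records exercise data. These support users and may show who stopped. They do not supply a usability rating from those who leave.
- The SUS is one of seven secondary outcomes, the bands are not a pass/fail rule, and the study is meant to inform later research. This limits the weight of the point without removing it.

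**Conclusion.** The point holds as a limited design weakness. Early withdrawers would give no stated post-use SUS for an outcome tied to a stated aim, so the mean **may** be biased upward. A reader might go further and conclude that it **is** biased upward or that the ease-of-use answer will be wrong. The documents do not support that, because they give neither a withdrawal rate nor any indication of how those who leave would score.

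Under the assumed values, the bias runs from 1.5 to 10.5 points for 3 to 9 non-raters of 30 with a rater mean of 75. Whether the mean crosses 70 depends wholly on those assumptions.

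Independently of any withdrawal, the score describes technology-willing, tablet-familiarised attendees of one community centre. It does not support a statement about older people in general. This part rests on the eligibility and setting text alone. The primary outcome is not affected.

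**What to change.** 1. Administer the SUS when a participant stops using the platform or withdraws, in a nurse contact already planned, as well as at week 8. Base the ease-of-use result on everyone who started.
2. State the SUS timing, and do not treat a baseline SUS taken before home use as one half of a paired before-after test. Report the post-use score descriptively against the bands.
3. Count the people who decline at screening because of the technology, and report that number beside the score.
4. Word the ease-of-use conclusion for technology-willing, tablet-familiarised community-centre attendees.

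Breaking the SUS down by prior tablet use is not recommended, because it would add little with about 30 people.

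**Cost:** the ten SUS statements for the few who stop, one column in the screening log and a few sentences of text. No extra visits or staff are needed. The article reports that recruitment was suspended and not yet restarted, so the change could be in place before the first participant.

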### Materials

The data collection instrument includes sociodemographic or clinical variables and functional evaluation variables. Lower limb strength and muscle resistance are the functional variables assessed through the 30-second CST, and mobility is evaluated with the TUGT (normal step). These functional tests, together with the 4 SBT, help evaluate the risk of a fall, which is also assessed with the fall risk screening tool using its inertial sensors to obtain information on the movements performed by the participant and related characterization. The risk of fall is then determined from parameters calculated after processing the signal from the inertial sensors during the execution of functional tests, such as walking, sitting, and standing (Figure 2).

The participants’ functional capacity for instrumental activities of daily living (IADL) is assessed using the Lawton and Brody tool, FES-I, SUS, and HFPC (Figure 3).

**Figure 2 figure2:**
[figure not shown]
Fall risk screening tool.

**Figure 3 figure3:**
[figure not shown]
Data collection instrument.

### Tests

The following tests will be performed to assess the outcome variables of the study.

#### Lower Limb Strength

The 30-second CST is a quick test that does not require a dynamometer, training, or special equipment. It is used to evaluate the strength of the lower limbs by counting the number of times the individual stands and sits in 30 seconds [14,24]. Therefore, the performance in the 30-second stand-and-sit test is used as a measure of the strength and muscle resistance of the lower limbs, specifically of the extensor muscles of the knee [25,26].

#### Mobility

The TUGT (normal step) measures, in seconds, the time an individual takes to stand up, walk a distance of 3 meters, return, and sit down in the same chair. Individuals who complete the test in <20 seconds are reportedly independent in manual handling transfer, and individuals who complete the test in >30 seconds tend to be dependent for this task [27]. It has also been reported that the time spent on the TUGT performance is related to scores on the Berg Balance Scale (*r*=–0.72), walking speed (*r*=–0.55) and the Barthel ADL index score (*r*=–0.51). The TUGT is a useful and practical measure for assessing mobility in the frail elderly and is easy and quick to apply without the need for special equipment or training.

#### Static Balance

The 4 SBT is used to track impairments in the static balance of the elderly. Several authors have reported that the test has excellent test-retest (*r*=0.97) and interevaluator reliabilities (kappa=0.92) [28,29]. According to the guidelines issued by the Centers for Disease Control and Prevention, the test must first be demonstrated to the participants by a nurse or physiotherapist, allowing the participants to perform a trial test to ensure correct performance. Participants are instructed to perform the four 10-second stages of the test sequentially. If the participant manages to perform 1 stage in 10 seconds, without moving the feet, losing balance, or needing support, the participant can move on to the next stage. If the participant fails this test, it is terminated [30]. The success of fall prevention programs is measured by comparing the positions achieved in 10 seconds in the pre- and postprogram evaluations [17].

Participants are instructed to be in an orthostatic position and perform the 4 different feet positions sequentially: position 1 is a side-by-side stance; position 2 is a semitandem stance (preferred foot forward with the instep foot touching the hallux of the other foot); position 3 is a tandem stance (one foot in front of the other, the heel of one foot touching the toes of the other); position 4 is a one-legged stance (using the preferred leg for support).

The final score will be the number of positions that are completed without loss of balance. Participants who cannot maintain position 3 for 10 seconds have a high risk of falling [30].

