### Setting

This study will be deployed in the city of Porto, within the area of Bonfim at the council in which the care center is located. The population of Bonfim is about 24,265 people, of which 27.1% are elders (>65 years old), according to the 2011 census. This day center is located in an area of the city with an aging population, in which people aged 65 years and over represent 36.3% of the population and young people represent 18.2% of the population, with a total dependency index of 54.9%.

The elderly institution has 2 modalities: long-term hospitalization (for very dependent people) and a community center. The participants for this intervention will only be enrolled from the elderly who attend the activities in the community center but live in their own homes. The intervention will take place in the houses of the participants.

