#### Technological Platform

The technological solutions to be used to support the physical exercise program consist of 3 applications.

The FallSensing Clinical App requires the use of a Windows computer, 2 wearable devices with inertial measurement units, and a pressure platform to obtain information about the movement and balance of the user while performing the CST, TUGT, and 4 SBT. The application also allows the creation of a personal profile for each participant, in which the participants’ answers to questionnaires for the assessment of several risk factors for falls, such as the IADL or FES-I home hazards questionnaires, can be saved. Additionally, the application will enable the prescription of OEP exercises and scheduling for each participant through a dedicated exercise prescription interface. This exercise prescription will be sent automatically to the FallSensing Home application.

The interactive FallSensing Home App, based on the OEP, aims to improve physical functionality. The application features 8 exercises from the program that are static, easy, and well accepted, with interactive feedback for the execution of the movement. The application can also motivate participants who perform the exercises at home. The application requires an Android tablet, support for the tablet, 2 wearable inertial devices, and the respective chargers. The users will be guided through a weekly exercise plan, which they will be able to select through the tablet interface where the instructions for executing each exercise will be presented, as well as an interface with visual feedback during the execution of each exercise (Figures 4 and 5).

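### The secondary balance outcome counts only completed stances (0-4), so improvement within a stance goes unscored; testing seconds held would be more sensitive at little cost

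*Protocol article*

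**What the plan says.** Balance is named in the abstract's Objective. Outcome Measures lists the 4-stage balance test as a secondary outcome; the primary is the timed-up and go test.

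Static Balance fixes the procedure and the score. "Participants are instructed to perform the four 10-second stages of the test sequentially", and the test ends at the first stance failed. Change is read the same way: "The success of fall prevention programs is measured by comparing the positions achieved in 10 seconds in the pre- and postprogram evaluations". The score is then: "The final score will be the number of positions that are completed without loss of balance".

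Recruitment and Sample sets the mobility rule ("The inclusion criteria are able to walk independently"). It lists no criterion on balance, fall history or fall risk, and sets a minimum of 30 participants. Statistical Analysis plans a paired Wilcoxon test for quantitative variables at P<.05. Technological Platform says that the clinical application uses wearable devices and "a pressure platform to obtain information about the movement and balance of the user while performing the CST, TUGT, and 4 SBT". No measure from that equipment is listed as a balance outcome.

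**The concern.** The score has five possible values and two blind spots.

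- **Coarseness.** A one-leg hold that rises from 4 s to 9 s scores 3 at both visits.
- **Ceiling.** A participant who scores 4 at baseline can only stay there or fall.

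Both produce zero differences, which carry no information about change in the usual Wilcoxon signed-rank test. With about 30 participants, few informative pairs may remain. Entry does not select people with a balance deficit, so nothing in the design limits the number who start at 4. The Conclusions say that the findings will feed the design of later studies. A non-significant balance result that came from the scoring could be read there as absence of effect.

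**Working it through.** The protocol states no power, effect size, standard deviation or baseline distribution for this test, so there is no figure to reproduce. The check is a sensitivity analysis.

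**From the protocol:** n = 30 (minimum); score 0-4; 10 s per stance; stop at first failure; paired Wilcoxon; alpha 0.05. Two-sided testing is assumed.

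**1. How many informative pairs are needed.** Suppose every non-zero change is one stance. With m non-tied pairs, all improvements:
- Exact two-sided P = 2 × 0.5^m. For m = 5 this is 0.0625 and for m = 6 it is 0.031, so six are needed.
- Large-sample P without continuity correction uses z = m/√m = √m. For m = 4, z = 2.00 and P = 0.046, so four suffice.

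The protocol does not say which P value will be used, so both are shown below.

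**2. Effect of the ceiling on the count.** Let c be the share at 4 at baseline and q the chance that any other participant gains one stance. Power of the exact test, n = 30, q = 0.4 (assumed):

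| c | 0 | 0.2 | 0.4 | 0.5 | 0.6 | 0.7 |
|---|---|---|---|---|---|---|
| nobody declines | 0.99 | 0.95 | 0.76 | 0.57 | 0.35 | 0.14 |
| 5% of all decline | 0.82 | 0.63 | 0.37 | 0.24 | 0.12 | 0.05 |

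The answer depends on c, which the protocol does not give.

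**3. Count against seconds held.** Assumed model: one-leg capacity is lognormal with median 5, 8 or 12 s and between-person log-SD 0.9. Tandem capacity is 4 times one-leg capacity, and everyone passes the first two stances. Within-person log-SD is 0.35, drawn separately for each stance and visit. Total seconds = 20 + min(tandem, 10) + min(one-leg, 10), with the last term 0 if tandem is failed. There were 2,000 simulated trials per row (Monte Carlo standard error at most √(0.25/2000) = 1.1 points).

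A second set uses within-person log-SD 0.158. That corresponds to a reliability of 0.81/(0.81 + 0.025) = 0.97, the test-retest figure in Static Balance. The first set gives 0.81/(0.81 + 0.1225) = 0.87. Applying that coefficient to log capacity is itself an assumption.

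Power (%) at medians 5 / 8 / 12 s:

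| Within-person log-SD | Gain | Count, large-sample P | Count, exact P | Seconds, large-sample P | Seconds, exact P |
|---|---|---|---|---|---|
| 0.35 | 30% | 39 / 35 / 31 | 28 / 24 / 17 | 71 / 61 / 47 | 71 / 60 / 46 |
| 0.35 | 50% | 73 / 70 / 60 | 62 / 58 / 40 | 96 / 90 / 78 | 96 / 90 / 77 |
| 0.158 | 30% | 69 / 62 / 52 | 40 / 31 / 18 | 100 / 99 / 94 | 100 / 99 / 93 |
| 0.158 | 50% | 95 / 91 / 83 | 82 / 71 / 51 | 100 / 100 / 99 | 100 / 100 / 99 |

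With no true change, rejection was at most 6% for either score.

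At log-SD 0.35 and a 30% gain, 24 / 41 / 57% started at the maximum and 71-79% had an unchanged count. Even with only 24% at the maximum, therefore, most counts did not move. Coarseness accounts for the rest.

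**4. Does seconds remove the ceiling?** No. In the same scenario 20 / 37 / 54% of pairs were still tied on total seconds, close to the share at the maximum.

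**5. Other assumptions.** Setting tandem capacity at 2 times one-leg capacity, or sharing the day's variation between stances, left seconds ahead in every scenario with a gain. The smallest gap at a 30% gain was 34% against 41% (median 12 s, both changes, log-SD 0.35, large-sample P).

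**The case against.** The count is a deliberate choice. Static Balance cites a source for judging programmes by stances achieved and reports good reliability for the test; no reliability is available here for summed seconds. That stands as a reason to keep reporting the count. Reliability does not show that a score responds to change.

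A reader might infer that most participants cannot register a change. The documents do not support this. Anyone who starts at 0-3 can still gain a stance, and walking independently does not imply a 10-second one-legged stance. Two features work against a ceiling: entry is open to "Participants aged 65 years or older who were living at home in the district of Porto, Portugal" with no upper age limit, and it excludes "current or previous participation in physical exercise programs in the last 6 months". The sample comes from "elderly who attend the activities in the community center but live in their own homes", which does not settle the matter either way. For 16 or more of 30 to start at 4, the probability is 0.006 if the true share is 30%, 0.10 at 40%, 0.43 at 50% and 0.83 at 60%.

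Nor do the figures support a prediction that the balance result will be a false negative. With a 50% gain the count has 60-73% power on the large-sample P at log-SD 0.35. At log-SD 0.158 it exceeds half for either gain on that P, though not on the exact P at a 30% gain.

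It would also be too strong to say that sensor information is thrown away. Materials uses inertial-sensor parameters to determine fall risk. The protocol speaks only of information on movement and balance and does not name sway.

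**Conclusion.** The point holds as a minor one. By the stated scoring rule, gains within a stance are not counted and a baseline score of 4 cannot rise. Under the assumed inputs the count has less power than seconds held in every scenario with a true gain: 17-39% against 46-71% for a 30% gain at within-person log-SD 0.35. With log-SD 0.158 the gap is wider in five of the six matched comparisons for that gain. In the sixth (median 5 s, large-sample P) it is about the same, 31 against 32 points.

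The capacities, gains and variances are assumptions, and the share at the ceiling is unknown. The sizes are therefore illustrative; the direction is not sensitive to the variants tried. The primary analysis is untouched.

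**What to change.** - Keep the test procedure and record the seconds held in each stance, up to 10.
- Define the tested balance outcome as total seconds over the four stances (0-40 s), counting the time held in the failed stance and 0 for stances not reached. Compare it before and after with the planned Wilcoxon test.
- Still report the 0-4 count and the position-3 risk cut-off at both visits.
- Report the number scoring 4 at baseline. Total seconds cannot show improvement for these participants, so any balance measure that the pressure platform or sensors provide during this test may be reported as supporting information.

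The cost is a short change to the outcome definition and a recorded time per stance, with no new test or equipment. It should be made before data collection, because unrecorded hold times may not be recoverable. The downside is that the tested balance result is no longer the standard 0-4 score, which is why that score stays in the report.
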